### Recruitment {15}

IRB-approved study flyers are posted in the opioid treatment program waiting and clinical rooms and instruct individuals interested in participating to notify study personnel to learn more about the study. Research personnel and treatment program staff also distribute study information to potentially eligible individuals. These individuals are approached subsequently by the study personnel and told about the study using a scripted verbal description of the study. All potential participants, regardless of how they learn about the study, are provided with detailed information about study procedures. Those who are subsequently screened, eligible to participate, and agree to participate are asked to provide written informed consent.

## Assignment of interventions: allocation

### Sequence generation {16a}

A complete random assignment procedure is used to allocate clusters to study arms. The package “randomizr” of the statistical software R was used for this assignment.

### Concealment mechanism {16b}

As an open-label study, both participants and researchers know about the assignment of participants to the treatment groups. The treatment assignment sequence was forwarded to the principal investigator of the project after generation.

### Implementation {16c}

The project statistician generated the treatment assignment sequence. The research coordinator informs participants to their allocation.

## Assignment of interventions: blinding

### Who will be blinded {17a}

Due to the nature of the study, participants and the investigator responsible for delivering group WCC are not blinded to group allocation. However, all participants are assigned a unique identification number at enrollment to ensure that research personnel responsible for analysis will be blinded to allocation status.

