## Data collection and management

### Plans for assessment and collection of outcomes {18a}

Data is derived through EMR abstraction and from questionnaires completed during study assessment visits. Data from all sources are matched by the participant’s unique study identification number and entered into one master electronic REDCap database. Data entry and checking is an ongoing process as the data become available. The final analytic dataset will be void of personal identifiers to protect the confidentiality of participants.*Medical record abstraction*: EMR data of participants and their children are abstracted by research personnel following participant enrollment into the study, the birth of a participant’s child, and at the 6-, 12-, and 18-month study visits. A standard data abstraction form is used.*Participant assessments*: All randomized study participants in both study arms will have a total of 5 assessment visits with research personnel. The first visits will occur immediately following enrollment into the study (baseline). For participants who enroll while pregnant, subsequent study assessment visits will occur prior to the participant’s child turning 1 month of age, and within 4 weeks of the participant’s child turning 6, 12, and 18 months of age. For participants who are not pregnant when they enroll, subsequent study assessment visits will occur at 1, 6, 12, and 18 months post-enrollment. At each assessment visit, participants will complete a set of standardized questionnaires in a private research room using traditional paper-and-pencil forms. No personally identifying information will be collected on the questionnaires. The 18-month study visit will also involve a 15-min observed free play session between the mother and child, which will be videotaped and subsequently coded according to standardized procedures using the *Keys to Interactive Parenting Scale* [23].*In-depth interviews*: Participants in the intervention arm will participate in semi-structured, individual in-person interviews at 9 and 18 months after their first group WCC session. These interviews will be conducted in a private research room, last 20–30 min, and be audio recorded and transcribed verbatim by a HIPAA compliant transcription service. During the session, participants will be asked to discuss things that they like and dislike about the group WCC program and how the program could be improved. Participants will be asked to report their experiences of receiving care in a group format, focusing on session structure, interaction with other mothers, and receiving specific information. Standardized interview question guides with prompts to engage participants in a fluid discussion will be used.

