### Confidentiality {27}

All participants will be assigned an anonymous study identification number at enrollment. Study IDs will be used on all instrumentation and will be linked to an individual’s identifying information by a master study key which will be maintained in hard copy locked in the principal investigator’s office. All hard copies of study files as well as videotapes of the recorded play sessions and audiotapes of the interview sessions and focus group discussions will be kept in locked cabinets in research personnel office. Data collection instruments (e.g., questionnaires, EMR abstraction tools), coded video data, and transcripts will omit names and identifiers that could potentially identify the participants. All electronic data files will be saved on a University password-protected, encrypted computer and be backed up daily. Documentation of data management procedures will be carefully maintained. No results will ever be reported in a personally identifiable manner.

Each participant randomized to group WCC will have the opportunity to privately discuss any concerns about her child with the pediatrician before the group visit begins. The group WCC model of care is designed to promote greater breadth and depth of discussion, as well as increased focus on maternal wellness and social determinants of health. Therefore, it is possible that group discussion may bring forth sensitive topics, for example, intimate partner violence that could cause psychological distress for participants. Prior to each group WCC visit, the pediatrician will review group rules including confidentiality and the use of the session as a “safe space.” Any participant experiencing significant distress as a result of the discussion will be escorted from the room by one of the co-facilitators, and an on-site nurse manager or social worker at the SUD treatment program will be notified. In the case information is disclosed during group discussions about child abuse or neglect, intent to harm self, or intent to harm others, the pediatrician will follow standard reporting procedures as required by law.

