## Statistical methods

### Statistical methods for primary and secondary outcomes {20a}

#### Quantitative data

Analyses will follow intent-to-treat principles, with participants analyzed according to randomized treatment assignment of the cluster in which they reside. Most analyses will use the individual participant as the unit of analysis, but because randomization is at the cluster level, model-based approaches that account for the correlation between individual participants within a cluster will be used.

Collected data will be summarized in tabular and graphic forms. Demographics and other study variables will be summarized by treatment groups. Mean (SD) or median (interquartile), as appropriate, will be used to describe numerical data, and frequency and percentage will be used to describe the distribution of categorical variables between treatment groups. Two-sample t-test, Mann–Whitney U test, chi-square test, and Fisher’s exact test will be used to compare the distribution of study variables between two-intervention groups as appropriate. Longitudinally collected data will be summarized by intervention groups and data collection time points.

Analysis of variance (ANOVA) and generalized linear and logistic regression models will be used to analyze outcomes measured at one time point, as appropriate. Trajectories of change for outcomes that are repeatedly measured over time will be examined using generalized linear mixed models (GLMMs) and linear, logistic, and negative binomial/Poisson regression models for continuous, binary, and count outcomes. Total scores and subscales from assessments will be used when applicable. The use of GLMM models will allow for an estimation of between-group differences in outcomes at each time point of measurement and will allow for an estimation of changes over time and time by group interactions while accounting for within-subject associations arising from the repeated measures. Clustering of participants will be accounted for in the GLMMs models by including cluster as a random or fixed effect and in the generalized models by using robust variance estimates. Potential covariates will be selected based on consideration of study arm balance and potential confounders for an outcome previously reported in the literature.

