### Methods for additional analyses (e.g., subgroup analyses) {20b}

Potential differences in treatment effects across influential participant characteristics (e.g., maternal age, number of children, infant sex) and group WCC characteristics (e.g., group size) will be assessed. A scale variable that will reflect a participant’s attendance level at group WCC visits will be created and included in the models to evaluate whether there is a “dose–response” intervention effect. Analyses will follow intent-to-treat principles, with participants analyzed according to randomized treatment assignment. In addition, a “per-protocol” analysis will be performed; the per-protocol analysis would include only participants who were adherent to their assigned study regimen and completed 75% of the recommended number of WCC sessions by 18 months of follow-up.

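### Participant ID numbers do not mask the arm, so the stated blinding of analysis personnel is not secured by the means given and conflicts with the section on concealment.

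*Protocol article*

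**What the plan says.** All references are to the protocol article.

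- **Who will be blinded {17a}** concedes that participants and the investigator delivering group care are unblinded. It then makes an exception for the analysts and gives one means: "all participants are assigned a unique identification number at enrollment to ensure that research personnel responsible for analysis will be blinded to allocation status".
- **Concealment mechanism {16b}**: "As an open-label study, both participants and researchers know about the assignment of participants to the treatment groups". The sequence went to the principal investigator once generated.
- **Implementation {16c}**: "The project statistician generated the treatment assignment sequence".
- **Confidentiality {27}** gives the ID its other use: "Study IDs will be used on all instrumentation and will be linked to an individual’s identifying information by a master study key".
- **Plans for assessment and collection of outcomes {18a}** uses it for record linkage: "Data from all sources are matched by the participant’s unique study identification number". Interviews are held in the intervention arm only.
- **Trial design {8}** allocates 26 consecutive birth-month clusters, 13 per arm. **Statistical methods {20a}** carries cluster into the models.
- **Statistical methods {20a}**, on adjustment: "Potential covariates will be selected based on consideration of study arm balance", together with confounders already reported in the literature.
- **Methods for additional analyses {20b}**: a scale for "attendance level at group WCC visits will be created and included in the models", and effect modification by group size.

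**The concern.** The article claims a property (analysts do not know the arm) and names a tool (the participant ID) that cannot produce it. A fuller plan could add detail, but it would not make this sentence correct: the reason it gives for the blind is the wrong reason.

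Two things are at stake. First, this is the only blind claimed in an open-label trial, so the results paper may describe a blinded analysis on the strength of a step that only pseudonymizes. Second, {20a} states a data-dependent rule, under which covariates depend partly on the balance seen between the arms. An analyst who knows which arm is which, and can see the treatment estimate under different covariate sets, could drift toward the set that favors the intervention without intending to. Masking the direction until the choice is fixed protects against that.

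**Working it through.** **1. What the ID does.** Set the three uses side by side. In {27} the ID replaces the name, and a locked key links the two. In {18a} it joins records from different sources into one database. In {17a} it is said to blind analysts to allocation. The first two are real functions of an ID. The third does not follow, because a file with one ID per row and an arm column, or a cluster column that can be mapped to arm, shows allocation just as clearly as a file with names. The article describes no coded arm label, separate data handler or restricted file.

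**2. Consistency of the neighboring sections.** {16b} says researchers in general know the assignment. {16c} says the project statistician made the sequence. {17a} says analysis personnel are blinded. The three agree only if the analysts are people other than the researchers meant in {16b} and other than the sequence generator. The article does not say so.

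**3. Where the arm could show through.** Arm is fixed by birth-month cluster ({8}). Anyone who holds the sequence and sees calendar birth month or birth dates can read the arm. Group attendance ({20b}) exists in one arm only, as do group size ({20b}) and interview records ({18a}), so these fields reveal the arm even without the sequence. In this design masking takes deliberate steps, and assigning IDs is not one of them.

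**4. Size, as an illustration.** The plan gives no figure for this. The starting point is its two-tailed 0.05 level ({20a}), taken per test before the Benjamini–Hochberg adjustment: 2.5% false benefit plus 2.5% false harm. The sample-size figures are not affected.

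Assumptions, none from the documents: *k* candidate specifications, null test statistics equicorrelated at *ρ*, and the statistic most favorable to the intervention always kept. Write z_j = √ρ·W + √(1−ρ)·e_j, with W and e_j independent standard normal. Then

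- false benefit = 1 − E[Φ((1.96 − √ρ·W)/√(1−ρ))^k]
- false harm = E[Φ((−1.96 − √ρ·W)/√(1−ρ))^k]
- total = the sum of the two.

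Numerical integration gives:

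| k | ρ | False benefit | False harm | Total |
|---|---|---|---|---|
| 1 | – | 2.5% | 2.5% | 5.0% |
| 2 | 0.90 | 3.5% | 1.5% | 5.0% |
| 4 | 0.95 | 4.0% | 1.3% | 5.3% |
| 4 | 0.90 | 4.7% | 0.9% | 5.6% |
| 4 | 0.80 | 5.7% | 0.5% | 6.2% |

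Directed selection mainly moves error from the harm side to the benefit side. At k = 4 and ρ = 0.9, false benefit is multiplied by 4.7/2.5 ≈ 1.9, while the total rises by only about 0.6 percentage points.

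**The case against.** **The sections can be read together.** {16b} is a general open-label statement and {17a} carves out an exception for analysts. That reading is possible, and it limits how far the contradiction can be pressed. It does not repair the ID-number reasoning.

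**A reader might infer that no blind exists and that the analyst can read every participant's arm.** The article does not support that. It does not say that the sequence generator does the analysis, or that calendar birth month is the cluster label; an arbitrary label would serve the models. {18a} says the final analytic dataset carries no personal identifiers. Attendance and group size belong to the additional analyses, and nothing says they are in the file when the primary models are chosen. This part of the objection stands: the blind is unsecured, not shown to be absent.

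**A reader might also put the inflation at about 9.4%**, the chance that the largest |z| of 4 specifications at ρ = 0.9 exceeds 1.96. That figure describes searching in both directions. It needs no knowledge of the arm, and an analyst working with A/B codes could do it equally well, so it does not measure what masking protects against. The directed figures under working are the relevant ones.

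**Open choices belong to the analysis plan.** This stands for the imputation method, the type of test, and cluster as a random or fixed effect, so none of these is counted here. The covariate rule differs because it is written down and depends on the data. Even so, balance can be judged under coded arms, and the rule also names literature-based confounders.

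**Conclusion.** The point holds in a limited form. {17a} presents pseudonymization as masking. The claim conflicts with {16b} on a plain reading, and {16c} leaves the sequence generator unseparated from the analysis role. That is an error in the stated text and is worth correcting before any results are described as analyzed blind.

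The consequence is moderate. Under k = 4 and ρ = 0.9 with always-favorable selection, false benefit goes from 2.5% to about 4.7% and total error from 5% to about 5.6%. Over the settings tried, false benefit runs from 3.5% to 5.7% and the total from 5.0% to 6.2%. These are worst cases on assumed inputs, not predictions for this trial, and they apply only if the person choosing covariates in fact knows the arm, which the article neither states nor rules out.

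**What to change.** Replace the ID-number sentence in {17a} with a procedure that masks:

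- Existing staff outside the analysis prepare the file with arm coded A/B and clusters given arbitrary codes.
- Birth dates are reduced to ages.
- Group attendance and group-size fields are withheld until the covariates and primary models are locked and dated. Arm balance can still be examined under the A/B codes.
- The holder of the allocation sequence does not make those choices.
- The code is then broken, and the dose-response and group-size analyses follow.

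Amend {16b} and {16c} to say which researchers know the assignment and who holds the sequence, so that {16b}, {16c} and {17a} agree. If this will not be done, delete the claim and report the analysis as unblinded.

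The cost is recoding a file of 108 dyads and holding back a few variables, with no new staff. The downside is a short delay before the attendance-based analyses can start. The locking step matters as much as the codes, because A/B labels alone do not stop a search in both directions.

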## Data collection and management

### Plans for assessment and collection of outcomes {18a}

Data is derived through EMR abstraction and from questionnaires completed during study assessment visits. Data from all sources are matched by the participant’s unique study identification number and entered into one master electronic REDCap database. Data entry and checking is an ongoing process as the data become available. The final analytic dataset will be void of personal identifiers to protect the confidentiality of participants.*Medical record abstraction*: EMR data of participants and their children are abstracted by research personnel following participant enrollment into the study, the birth of a participant’s child, and at the 6-, 12-, and 18-month study visits. A standard data abstraction form is used.*Participant assessments*: All randomized study participants in both study arms will have a total of 5 assessment visits with research personnel. The first visits will occur immediately following enrollment into the study (baseline). For participants who enroll while pregnant, subsequent study assessment visits will occur prior to the participant’s child turning 1 month of age, and within 4 weeks of the participant’s child turning 6, 12, and 18 months of age. For participants who are not pregnant when they enroll, subsequent study assessment visits will occur at 1, 6, 12, and 18 months post-enrollment. At each assessment visit, participants will complete a set of standardized questionnaires in a private research room using traditional paper-and-pencil forms. No personally identifying information will be collected on the questionnaires. The 18-month study visit will also involve a 15-min observed free play session between the mother and child, which will be videotaped and subsequently coded according to standardized procedures using the *Keys to Interactive Parenting Scale* [23].*In-depth interviews*: Participants in the intervention arm will participate in semi-structured, individual in-person interviews at 9 and 18 months after their first group WCC session. These interviews will be conducted in a private research room, last 20–30 min, and be audio recorded and transcribed verbatim by a HIPAA compliant transcription service. During the session, participants will be asked to discuss things that they like and dislike about the group WCC program and how the program could be improved. Participants will be asked to report their experiences of receiving care in a group format, focusing on session structure, interaction with other mothers, and receiving specific information. Standardized interview question guides with prompts to engage participants in a fluid discussion will be used.

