### Intervention description {11a}

As the framework for the group WCC intervention, we leveraged Centering®, a model of care delivery developed by The Centering® Healthcare Institute [15]. Centering® seeks to shift the paradigm of health services from individual to group care, bringing patients out of a traditional office and into a group setting where they learn from their providers and each other. Each group session has planned core content, with consistency of providers across all sessions, and 2 h per session for health assessment, interactive learning, and community building. Instead of didactic education, providers use facilitative leadership, encouraging patients to fully engage in their care and raise issues of importance to them.

*CenteringParenting*is the pediatric adaptation of Centering® and is based on the American Academy of Pediatrics recommended schedule of visit periodicity, including developmental milestone assessments, anticipatory guidance, and immunizations [16]. In addition to standard WCC topics focused on infant health and development, *CenteringParenting*places emphasis on maternal wellness including nutrition and exercise, family planning, stress reduction, and interpersonal relationships [14, 17].

Participants who enroll into CHAMPS during pregnancy and are randomized to the intervention arm initially receive routine individualized well care after birth hospital discharge. This consists of an initial 30-min newborn visit usually within 2–3 days after discharge at the affiliated pediatric primary care office, with any additional 15-min visits in the first few weeks of life as needed, i.e., for jaundice or a weight check. Beginning with the 1-month WCC visit, mother-infant dyads grouped by birth month (anticipated *n* = 3–5 per group) are scheduled for WCC together, with subsequent visits occurring at the American Academy of Pediatrics recommended intervals (2, 4, 6, 9, 12, 15, and 18 months of age). Group WCC visits occur on-site at the opioid treatment program. Infants with an extended hospitalization beyond 1 month are eligible to join into a later group session if needed.

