#### Primary outcomes

*WCC engagement*: measured as both utilization and experience of WCC.*WCC utilization*: The total number of age-appropriate WCC visits during the 18-month study period will be abstracted from the pediatric electronic medical record (EMR). Adequacy of WCC during this time will be dichotomized as “adequate” (completes the recommended number of WCC visits) or “inadequate” (does not complete the recommended number of WCC visits). This definition is adapted from the Health Plan Employer Data and Information Set (HEDIS) measure for WCC [20]. The mean number of age-appropriate WCC visits during the 18-month study period and the proportion of participants with adequate WCC over the 18-month study period will be compared between the 2 study arms.*WCC experience*: The *Promoting Healthy Development Survey* (PHDS) [21], a 43-item standardized, validated parent survey designed to measure the quality and content of care for children 3–48 months, is completed by participants at the 6-, 12-, and 18-month follow-up assessment visits. The PHDS will be used to evaluate participants’ perceptions of their child’s WCC, including (1) anticipatory guidance—whether the mother received age-appropriate guidance; (2) developmental surveillance—whether the mother was asked about concerns about her child’s learning, development, or behavior, and if concerns were addressed; (3) family-centeredness—whether the mother felt her perspective was heard and valued; (4) family risk assessment—whether the mother was asked about issues in the family (e.g., substance use, emotional support); and (5) helpfulness of care—how helpful the care provided was in specific aspects of parenting (e.g., understanding child behavior). Multiple survey items are used to calculate a score for each component of care evaluated and these composite measures have been previously tested for internal consistency. The mean score for each component of care at each time point will be compared between the 2 study arms.*Parenting knowledge*: The medical literature was reviewed for previously validated questions used to assess parental knowledge about the care and development of intrauterine opioid-exposed infants; no prior questions were identified. Therefore, a survey instrument includes investigator-developed questions specific to this area, (e.g., “Breastfeeding increases the chance your baby will have opioid withdrawal symptoms: Agree/Disagree/Not Sure”), as well as questions from the Knowledge of Infant Development Inventory (KIDI) [22]. The KIDI is a widely used measure of parenting knowledge designed as a diagnostic tool for high-risk parents. The KIDI consists of 58 items grouped into four categories (norms and milestones, principles, parenting, and health and safety) that tests mothers’ knowledge of children’s development and parenting of children from birth through 36 months of age. Items are measured on a 5-point Likert scale with higher scores indicating correct knowledge and developmentally appropriate expectations. In addition to a total knowledge score calculated by summing the number of correct items and calculating an average, four KIDI subscale scores and a knowledge of infant opioid exposure score will also be generated. The total and subscale score at 18 months will be compared between the 2 study arms. The mean change in scores from baseline to 18 months follow-up will be compared between the two study arms.*Maternal-child interaction quality*: This is directly assessed using video-recorded mother/child free play at an 18-month follow-up assessment visit. Interactions are coded by certified scorers using the Keys to Interactive Parenting Scale (KIPS) [23]. KIPS assesses 12 parenting behaviors using quality ratings ranging from 1 to 5 within three domains sub-scale domains: building relationships, promoting learning engagement in language experiences, and supporting confidence. A total score is generated by summing the 12 items and calculating an average to indicate low, moderate, and high-quality parenting behavior. The total and subscale score at 18 months will be compared between the 2 study arms.

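### Intervention-only interviews about experience of care precede the 12-month PHDS for mothers enrolled in pregnancy and could affect responses in one arm

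*Protocol article*

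**What the plan says.** The section Plans for assessment and collection of outcomes {18a} sets a common schedule for both arms: "All randomized study participants in both study arms will have a total of 5 assessment visits with research personnel". For women who enroll while pregnant, the later visits fall "within 4 weeks of the participant’s child turning 6, 12, and 18 months of age", after one before the child reaches 1 month. For those already parenting, "subsequent study assessment visits will occur at 1, 6, 12, and 18 months post-enrollment".

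The same section then adds a contact for one arm: "Participants in the intervention arm will participate in semi-structured, individual in-person interviews at 9 and 18 months after their first group WCC session". Each interview lasts 20 to 30 minutes. In it, "participants will be asked to discuss things that they like and dislike about the group WCC program and how the program could be improved". Mothers also report on receiving care in a group, "focusing on session structure, interaction with other mothers, and receiving specific information".

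Under Primary outcomes, experience of well child care (WCC) is measured by the PHDS, which "is completed by participants at the 6-, 12-, and 18-month follow-up assessment visits". Its components include whether guidance was given, whether the mother felt heard, and how helpful the care was. Mean component scores are compared between arms at each time point.

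The article does not say whether an interview comes before or after the questionnaires due around the same time.

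**The concern.** The PHDS asks a mother to judge her child's well child care. The interview asks intervention mothers, and only them, to think through and voice a judgement of that same care. If it comes first, one arm rates its care after a structured evaluation of it and the other arm does not. Participants know their allocation, so nothing masks this difference.

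Interview exposure goes with arm. At a time point that follows the interview, the analysis therefore cannot readily separate an effect of group care on reported experience from an effect of having been interviewed about it. Scheduling can remove the problem at 12 months; modelling cannot.

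**Working it through.** **Plan's own figure.** The Sample size section gives 80% power for a standardized difference of 0.54 with 54 per arm, two-sided 0.05. A noncentral t calculation gives 0.794 and the normal approximation 0.801, so the figure reproduces. This point does not dispute it. The check that matters is the calendar.

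**Mothers enrolled in pregnancy.** The Intervention description section fixes the first group session: "Beginning with the 1-month WCC visit, mother-infant dyads grouped by birth month" are seen together.

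- First interview: 1 + 9 = 10 months of age.
- Second interview: 1 + 18 = 19 months of age.
- Four weeks is 28 / 30.4 = 0.92 months. The 12-month window is 12 ± 0.92, or 11.08 to 12.92 months. The 18-month window is 17.08 to 18.92 months.
- First interview to the 12-month PHDS: 11.08 − 10 = 1.1 to 12.92 − 10 = 2.9 months.
- First interview to the 18-month PHDS: 7.1 to 8.9 months, about 8.
- The second interview falls just after the 18-month window closes.

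A mother whose first session is the 2-month visit would be interviewed at 2 + 9 = 11 months, still before the window. If it is the 4-month visit, the interview is at 13 months, after the window.

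**Mothers enrolled after birth.** Their assessments run from enrollment. Let L be the months from enrollment to the first group session; L is not stated.

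- First interview: 9 + L months after enrollment. It precedes the nominal 12-month visit if L < 3 and the 18-month visit if L < 9.
- Second interview: 18 + L months, at or after the nominal 18-month visit.
- Scheduled WCC visits are 1 to 3 months apart, so L between 0 and 3 is a reasonable assumption. It puts the first interview at 9 to 12 months after enrollment.

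**Which primary measures are exposed.**

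- 6-month PHDS: not exposed, since every first interview comes later.
- 12-month PHDS: exposed for mothers enrolled in pregnancy, and for the others if L < 3.
- 18-month PHDS: follows the first interview, but at a distance of about 8 months for mothers enrolled in pregnancy.
- Parenting knowledge at 18 months: scored on correct answers, so less open to a shift of this kind.
- WCC utilization: abstracted from the medical record.
- Keys to Interactive Parenting Scale (KIPS): scored from video by certified coders.

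**Illustration of size, by assumption only.** The documents give no figure for a reporting shift. Suppose there is no true effect, 54 per arm, all intervention mothers are exposed, and one arm's mean moves by b standard deviations. The two-sided t-test then has noncentrality b × √(54/2) = 5.196b.

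| Assumed b | Noncentrality | Rejection rate |
|---|---|---|
| 0 | 0 | 5% |
| 0.1 | 0.52 | 8% |
| 0.2 | 1.04 | 18% |
| 0.3 | 1.56 | 34% |

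This is one unadjusted comparison with no clustering. The two-sided rate is the same whichever way the shift goes. If only some mothers are exposed, the mean shift shrinks in proportion.

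**The case against.** Interviewing only the intervention arm about a group program is ordinary process evaluation, since controls have no group program to discuss. The order of tasks within a visit is also a detail that a protocol article can leave to the full protocol. Both points stand, so the missing within-visit order is weak evidence by itself. The 9-month interview, however, is a stated date, and for mothers enrolled in pregnancy that date puts it ahead of the 12-month PHDS.

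A reader might infer more than the documents support:

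- **That the interviews favour the intervention.** They ask for dislikes and improvements as well as likes. Inviting criticism could lower ratings as easily as raise them.
- **That an effect on responses is established.** Nothing in the article shows or sizes one. Questionnaires are completed on paper in a private room, which limits social desirability, and the article does not say who conducts the interviews.
- **That the second interview contaminates the 18-month outcomes.** As scheduled, it falls at or after the nominal 18-month visit. An order rule matters mainly for late visits and for mothers whose group care began close to enrollment.
- **That the added contacts improve follow-up in one arm.** The retention strategies in the article are not arm-specific, and intervention mothers already attend repeated two-hour sessions on-site. The documents give no basis for a retention claim.

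**Conclusion.** The point holds as a modest, cheaply avoided weakness. A one-arm research contact whose content overlaps a primary self-report measure is scheduled about 1 to 3 months before the 12-month PHDS for mothers enrolled in pregnancy, taking the first group session at 1 month of age. For mothers enrolled after birth the same holds if their first group session is less than 3 months after enrollment. The share of participants affected cannot be worked out from the article.

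The direction and size of any effect are unknown; the rejection rates tabulated above rest wholly on assumed shifts. The 18-month PHDS is exposed only remotely, and the 6-month PHDS, medical-record utilization and KIPS are largely untouched. No sample-size or power figure changes, and the trial's validity does not turn on this.

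**What to change.** In Plans for assessment and collection of outcomes {18a}, tie the interviews to the assessment visits and state the order:

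- hold the first interview directly after the 12-month questionnaires are completed;
- hold the second only after the 18-month questionnaires and the free-play video are completed.

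This needs no added visit, because each interview can follow the assessment on the same day. It leaves the 6- and 12-month PHDS free of any interview in both arms, so those two time points serve as the interview-free comparison.

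The costs are small. For mothers whose group care began at 1 month of age, first-round feedback arrives about 12 − 10 = 2 months later, and some visits run 20 to 30 minutes longer. The change does not clear the 18-month PHDS: the first interview would still precede it, by about 6 months rather than about 8.
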